### 6.3.2. Informed consent

Potential participants in the patient-reported outcomes/experience subcohort will be asked for their consent to retain and analyse their questionnaire responses, to be contacted again in future for follow-up questionnaires for this study, to access relevant information from their medical records held at their general practice and by NHS Digital and link this to their questionnaire responses.

In both online and pen-and-paper questionnaire formats, informed consent from willing patients will be obtained at the end of baseline questionnaire completion. For the online questionnaire this will be e-consent through the secure web-based interface hosted by Keele University; for the pen-and-paper it will be written consent; for those opting for telephone-supported completion of the questionnaire, the administrator will obtain verbal consent. Consent is being sought after patients have completed the online questionnaire to ensure that patients know what data they are providing before agreeing to it, this is in line with how patients will be completing the paper questionnaire. If a patient stops the initial online questionnaire part way through and changes their mind before they consent, the data they have provided will be destroyed.

The consent section will include mandatory statements that potential participants must confirm that they agree to in order to participate in the study.

As part of the baseline questionnaire, a minimal set of participant identifiable data will be collected in order to ensure an individual is correctly identified and that the right participant is identifiable for follow-up questionnaire completion. Both consent formats cannot be altered by the participant and will be dated either automatically by the web-based system for online completion or by the patient for manual completion. If the consent date is missing from the pen-and-paper consent form, the date the questionnaire was received will be added upon entry to the database by an administrator. If the patients' signature is missing from the pen-and-paper consent form, a completed consent form will be sought by following the incomplete consent procedure. Prior to seeking consent to study participation, all potential participants will have had the opportunity to access the Participant Information Sheet and contact a member of the study team. Patients who contact Keele CTU and provide consent over the telephone will be posted a hard copy of the Participant Information Sheet.

If potential participants decline the e-consent to take part in the study they will receive an onscreen notification thanking them for considering participation and explaining that they will not be contacted further. Those who do not consent to take part in the study will be notified all of their responses to the baseline questionnaire will be deleted.

We will also ask patients to provide either a) their mobile telephone number or email address (online questionnaire), b) their postal address and telephone contact number (postal questionnaire and from those completing over the telephone) for them to receive their follow-up questionnaires.

Patients completing the online consent will be given the option to obtain a copy of the consent form by emailing the study team.

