##### *Patient invitation*

Using the general practice's existing system for SMS texts to patients identified eligible consulters who have an active mobile phone number on the practice record will be sent an SMS text invitation from the general practice to take part in the research. Identified eligible consulters who do not have an active mobile phone number will be sent an invitation pack via Docmail. The invitation pack will include an invite letter (containing URL link to enable online questionnaire completion if so desired), baseline questionnaire with consent form, return pre-paid envelope and a Participant Information Sheet containing the contact details for Keele CTU should the patient wish to seek more information about the study or seek help to complete the questionnaire.

All potential participants receiving an SMS text invitation will be sent a reminder text approximately 48 hours after the initial text, which will include information on how to contact Keele CTU if they are unable to complete the questionnaire online.

Potential participants who do not respond will receive no further contact and will not be re-invited from the same practice, for example, if they revisit their GP within the study recruitment period.

When potential participants arrive at the online questionnaire, they will be provided with the opportunity to read a Participant Information Sheet and view an information video about the study.

The online questionnaire will be hosted by Keele University, with the option of telephone supported completion from a Keele CTU administrator or translation service. Respondents will be sent a follow-up questionnaire at 3 and 6 months after their initial consultation with a brief questionnaire sent in the intervening months' to capture pain intensity.

Participating GP practice will send an Excel file to the study team on a regular basis (approximately weekly), via NHS.net secure email. This file will contain the Organisational Code, NHS number, anonymised identifier, invite date and method of invitation for each patient sent an invitation to take part in the study. This file will be imported into the Study Management Application by a study administrator. When questionnaires are received into the CTU (online or paper) the information from their consent to take part in the study will be matched to the information from the import file, this will also ensure that the correct patient is taking part in the study.

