### *Brief monthly patient-reported questionnaires*

At months 1, 2, 4, and 5 following the index consultation the patient will be asked one question to report their pain intensity either using SMS text or postal questionnaire. Keele CTU has experience of using 2-way SMS text messages to collect outcome data in previous trials (Foster et al 2017,

Campbell et al 2016). The software development team within the CTU will support this data collection and will make use of an in-house bespoke database-driven Web-based system to manage the sending and receiving of SMS text messages. The participant will respond to Keele CTU via the third-party SMS provider. The CTU system will poll the third-party SMS provider for returned SMS text messages. On processing of returned SMS text messages, the system will import these into the study database and process the response according to the business logic defined in the project. Interception of the original message by a third party would reveal only what the questions were that were being asked, whilst interception of the response would only yield an alphanumeric string.

A telephone number will be provided to enable participants to contact Keele CTU if they have queries relating to the SMS text messaging during office hours.

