## **8 DATA HANDLING**

### **8.1. Data collection tools and source document identification**

Patient-reported data are to be captured through a secure online platform (Keele Health Survey) ensuring that all regulatory requirements are met, including the Data Protection Act 2018, UK General Data Protection Regulation (UKGDPR), NHS Information Governance, and Good Clinical Practice (GCP). Data will also be collected via paper questionnaires; these data will be entered manually into the online platform by a Keele CTU administrator. DOCMAIL is a standards-compliant hybrid mail service, providing document management and ISO 27001 secure mailings.

Patient-reported data will be collected at baseline and monthly for 6 months. Following a retrospective search at the GP practice, eligible patients with an active mobile telephone number registered at the GP practice will be sent a SMS text containing a URL link to an online questionnaire. Patients who do not have an active mobile telephone number at the GP practice will be sent an invitation pack including an invite letter, a Participant Information Sheet, a paper questionnaire, and a pre-paid return envelope. All patients who were sent a SMS text will be sent a reminder text approximately 48 hours after the initial text was sent. If patients do not respond after receiving this text reminder, there will be no further contact with them.

With regard to follow-up, patients will be sent one question at 1, 2, 4, and 5 months. This will either be sent via SMS text or a paper questionnaire. Where there is no response to the monthly question, one reminder SMS text or letter will be sent to the participant. If there is still no response from the participant, then they will continue on the follow-up pathway and will be sent the next month's follow-up questionnaire when it is due. A more substantial follow-up will be done at 3 and 6 months, where patients will be sent either a link via SMS text or email to another online questionnaire or posted a paper questionnaire. Where there is no response to the 3- and 6-month follow-up, two reminder SMS texts or emails or a postcard and then a paper questionnaire will be sent to the participant. If there is

still no response from the participant, at 3 months they will continue on the follow-up pathway, at 6 months there will be no further contact as this is the end of the study.

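### Online participants may give only an email address, but the pain question at months 1, 2, 4 and 5 goes only by SMS or post, so as written they can be reached for 2 of 6 follow-up pain scores

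*Protocol*

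**What the plan says.** **Contact details.** Section 6.3.2 gives two rules. Online completers supply "their mobile telephone number or email address (online questionnaire"). Other completers supply "their postal address and telephone contact number (postal questionnaire and from those completing over the telephone"). Someone who completes online and gives only an email address has therefore met the rule.

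**Who may complete online.** Patients with an active mobile number on the practice record are invited by SMS. The rest receive a posted pack, whose letter is described in Section 6.3.1 as "containing URL link to enable online questionnaire completion if so desired". Online completion is thus open to people with no mobile on record.

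**Monthly question.** In Section 6.3.3, under the brief monthly questionnaires, patients are "asked one question to report their pain intensity either using SMS text or postal questionnaire". Section 8.1 agrees: "patients will be sent one question at 1, 2, 4, and 5 months", followed by "This will either be sent via SMS text or a paper questionnaire". Section 6.1 names the same two modes. The single reminder for this question is an SMS or a letter (Section 8.1).

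**Questionnaires at 3 and 6 months.** Section 8.1 allows a link by SMS or email, or a posted form. For non-response it specifies "two reminder SMS texts or emails or a postcard and then a paper questionnaire will be sent to the participant".

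**Use of the data.** Table 1 schedules pain intensity at baseline and at every month to month 6. The Study Summary lists it among the expected main outcomes of the first primary objective. Section 7.3.1.3 models monthly pain with every follow-up response, and Section 7.3.1.4 uses monthly measures, where available, to impute missing 3- and 6-month MSK-HQ scores.

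**The concern.** The contact rule and the delivery rule do not fit together. Email is enough to enrol and to receive the 3- and 6-month questionnaires, but it is not a mode for the monthly question or its reminder. For an email-only participant the monthly score would be absent because the question was never sent, and not because the participant chose not to answer.

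The omission is consistent: three sections name SMS or post for the monthly question and none mentions email, whereas Section 8.1 does mention email for months 3 and 6. It is therefore hard to dismiss as one loosely worded sentence.

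At stake are four of the six follow-up points on a listed main outcome for each affected person, and part of the auxiliary information meant to support the MSK-HQ imputation. An analysis plan cannot recover answers to questions that were not sent.

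**Working it through.** **Inputs**
- Follow-up pain schedule (Table 1): months 1, 2, 3, 4, 5, 6, so 6 occasions.
- Brief monthly question (Sections 6.3.3 and 8.1): months 1, 2, 4, 5, so 4 occasions, by SMS or post.
- Full questionnaires (Section 8.1): months 3 and 6, so 2 occasions, by SMS link, email link or post.
- Consenting cohort (Section 7.1.1): 1,139.
- Share of participants giving email only: not stated.

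**Step 1: reproduce the cohort figure.** 7,300 × 0.80 × 0.15 = 876 consulters per practice per year. 876 / 4 × 26 = 5,694 in three months. 5,694 × 0.25 = 1,423.5 (stated as 1,424). 1,423.5 × 0.80 = 1,138.8 (stated as 1,139). The protocol's figures reproduce.

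**Step 2: reachable occasions by contact detail given, as written**

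| Detail given | Months 1, 2, 4, 5 | Months 3, 6 | Reachable |
|---|---|---|---|
| Mobile number (online) | SMS | SMS link | 6 of 6 |
| Postal address and telephone | Post | Post | 6 of 6 |
| Email only (online) | none named | Email link | 2 of 6 |

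The loss per email-only participant is 4/6 = 66.7% of follow-up pain scores.

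**Step 3: look for another source of contact details.** The file that each practice sends to the study team (Section 6.3.1) holds organisational code, NHS number, an anonymised identifier, invitation date and invitation method. It has no phone number or address. The items named for linkage and identity checks in Table 1 and Section 6.5 are NHS number, practice and date of birth. So even where the practice holds a mobile number, the protocol does not say that it reaches the trials unit.

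**Step 4: how the loss scales.** Let s be the email-only share of the 1,139. Scheduled scores without a route = 4 × 1,139 × s. All scheduled follow-up pain scores = 6 × 1,139 = 6,834. The values of s below are assumptions that show the scale; nothing in the protocol supports any one of them. People are rounded before multiplying by 4.

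| s (assumed) | People | Scores without a route | Share of 6,834 |
|---|---|---|---|
| 5% | 57 | 228 | 3.3% |
| 10% | 114 | 456 | 6.7% |
| 20% | 228 | 912 | 13.3% |
| 30% | 342 | 1,368 | 20.0% |

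These are scheduled scores. Some would have gone unanswered anyway: Section 7.1.1 assumes 50% response at follow-up. If that rate also held for the monthly question, which is a further assumption, the answers actually lost would be half of each figure, for example 456 × 0.5 = 228 at s = 10%.

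**Step 5: the last reminder at 3 and 6 months.** The sentence in Section 8.1 can be read in two ways. If the paper form is for postal participants only, it says nothing about online participants. If it is for every non-responder, it presupposes a postal address that Section 6.3.2 does not request from online participants. Neither reading, combined with Section 6.3.2 as it stands, gives an email-only participant a monthly route.

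**The case against.** The strongest reply is that the lack of a route is inferred from silence. Section 6.3.2 also mentions a small set of identifying data without itemising it, nothing stops a participant giving both a mobile number and an email address, and operational detail is left to a Data Management Plan that is not at hand. If the final paper form in Section 8.1 is meant for all non-responders, the authors may have intended to hold everyone's address. This is fair as to intention, but the protocol's explicit rule still accepts email alone. The finding is therefore about the protocol as written, and does not predict what the trials unit will do.

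A reader might also infer four stronger points, which the protocol does not support:

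- **Many participants are affected.** No share is given. People with an active mobile on record are invited by SMS, and the others receive a paper form with the web link as an option, so the email-only group may be small.
- **MSK-HQ is compromised.** It is collected at baseline, 3 and 6 months, and email is allowed at both follow-ups. The power statements in Section 7.1.1 and the analysis in Section 7.3.1.2 concern MSK-HQ. The effect on it is indirect, through imputation that uses monthly measures only where they exist. Pain at months 3 and 6 is also reachable, and the repeated-measures models keep people with missing occasions.
- **The comparison of disadvantaged with advantaged groups is biased.** The affected people completed online and use email, so they are not the digitally excluded group of Section 6.2. Those who complete on paper or by telephone give an address. No link to the comparison, and no direction, is shown.
- **Online non-responders cannot receive their paper reminder.** This depends on one of two readings of an ambiguous sentence.

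**Conclusion.** The inconsistency stands. Followed as written, Sections 6.1, 6.3.2, 6.3.3 and 8.1 leave an email-only online participant reachable for 2 of 6 follow-up pain scores, with the other 4 (66.7%) missing by design. The count comes directly from the protocol. It rests on one condition: that no contact detail reaches the study team beyond those the protocol describes.

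The consequence is loss of information on a listed main outcome (analysed under secondary outcomes in Section 7.3.1.3) and on a predictor in the MSK-HQ imputation. The overall size is unknown because the email-only share is not stated. Whether the loss biases any comparison, and in which direction, cannot be told from the protocol. The point is worth correcting because the remedy is simple and must be in place before the monthly questions go out.

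**What to change.** Make one of two changes:

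1. Add an email link as a delivery and reminder mode for the question at months 1, 2, 4 and 5. Email links are already planned for months 3 and 6.
2. Alternatively, require online participants to give a mobile number or a postal address, with email as an optional extra.

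Then align Sections 6.1, 6.3.2, 6.3.3 and 8.1. In Section 8.1, state whether the final paper questionnaire at 3 and 6 months is meant for online participants. If it is, Section 6.3.2 must ask them for a postal address; if not, the sentence should say that it applies to postal participants.

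The cost is a one-item email link on the existing platform, or one extra contact field on the consent page. Asking everyone for mobile number, email and postal address is more than the monthly question needs, and would sit badly with the aim in Section 6.3.2 of keeping identifiable data to a minimum.

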### 6.3.3. Data collection

**Table 1.** Schedule of assessments for the patient-reported outcomes subcohort

|                   | Timepoint (months) |    |    |    |    |    |    |
|-------------------|--------------------|----|----|----|----|----|----|
|                   | 0                  | +1 | +2 | +3 | +4 | +5 | +6 |
| MSK health |                    |    |    |    |    |    |    |
| Pain location     | x           |    |    |    |    |    |    |

|                                                                                                                                              |   |   |   |   |   |   |   |
|----------------------------------------------------------------------------------------------------------------------------------------------|---|---|---|---|---|---|---|
| Pain intensity (0-10 NRS) [19]                                                                                                               | x | x | x | x | x | x | x |
| Pain days [20]                                                                                                                               | x |   |   | x |   |   | x |
| Pain interference [20]                                                                                                                       | x |   |   | x |   |   | x |
| Duration of problem                                                                                                                          | x |   |   |   |   |   |   |
| Previous pain episodes                                                                                                                       | x |   |   |   |   |   |   |
| Previous surgery                                                                                                                             | x |   |   |   |   |   |   |
| MSK-HQ [21]                                                                                                                                  | x |   |   | x |   |   | x |
| Patient global rating of change                                                                                                              | x |   |   | x |   |   | x |
| Patient experience                                                                                                                    |   |   |   |   |   |   |   |
| Overall experience [22]                                                                                                                      | x |   |   |   |   |   |   |
| Communication [23]                                                                                                                           | x |   |   |   |   |   |   |
| Needs met [22]                                                                                                                               | x |   |   |   |   |   |   |
| Personalised plan                                                                                                                            | x |   |   |   |   |   |   |
| Healthcare utilisation                                                                                                                |   |   |   |   |   |   |   |
| HCP/service use for MSK                                                                                                                      | x |   |   | x |   |   | x |
| (Self-)management for MSK                                                                                                                    | x |   |   | x |   |   | x |
| General health                                                                                                                        |   |   |   |   |   |   |   |
| Height and weight                                                                                                                            | x |   |   |   |   |   |   |
| Health literacy [24]                                                                                                                         | x |   |   |   |   |   |   |
| Demographic/socioeconomic                                                                                                             |   |   |   |   |   |   |   |
| Age (date of birth)                                                                                                                          | x |   |   | x |   |   | x |
| Sex                                                                                                                                          | x |   |   | x |   |   | x |
| Ethnicity [25]                                                                                                                               | x |   |   |   |   |   |   |
| Perceived financial strain [26]                                                                                                              | x |   |   |   |   |   |   |
| Employment                                                                                                                            |   |   |   |   |   |   |   |
| Employment status                                                                                                                            | x |   |   | x |   |   | x |
| Job title (current/most recent)                                                                                                              | x |   |   |   |   |   |   |
| WPAI [27]                                                                                                                                    | x |   |   | x |   |   | x |
| Administrative                                                                                                                        |   |   |   |   |   |   |   |
| NHS number                                                                                                                                   | x |   |   |   |   |   |   |
| GP practice                                                                                                                                  | x |   |   |   |   |   |   |
| HCP Health care professional; MSK-HQ Musculoskeletal Health Questionnaire; WPAI Work Productivity and Activity Impairment (modified version) |   |   |   |   |   |   |   |

